## Abstract

**Background:**

Idiopathic sudden sensorineural hearing loss (ISSNHL) is a common form of deafness. Acupuncture has been used as a salvage therapy for ISSNHL in China since 200 BCE. However, the efficacy of acupuncture has not been confirmed in strictly controlled trials. We designed a randomized controlled clinical trial to evaluate the efficacy and long-term effects of acupuncture in patients with early ISSNHL.

**Methods/Design:**

In this randomized controlled clinical trial, we will enroll 124 participants with ISSNHL diagnosed 2 to 4 weeks prior to enrollment, who have shown little hearing improvement after routine Western medical treatment (i.e., corticosteroids). 62 of these participants will have flat audiogram and the other 62 will have a high-frequency drop audiogram; they will all take Methycobal while half of the flat type and half of the high-frequency drop type will also receive acupuncture treatments for 4 weeks in a four-group design. The primary outcome measure will be the effective rate of hearing improvement (defined as the proportion of patients with at least 15-dB improvement in the hearing loss frequency band). The secondary outcome will measure the improvements in Pure Tone Average, Word Recognition Score, and Tinnitus Handicap Inventory. The assessments of the participants will be made at baseline, after treatment (week 4), and at follow-up (week 28).

**Discussion:**

This study aims to explore the efficacy and long-term effects of acupuncture in patients with ISSNHL. This study will be a randomized controlled trial with strict methodology and few design deficits. If our study yields positive results, acupuncture could be recommended as a salvage therapy for patients with ISSNHL.

**Trial registration:**

Chinese Clinical Trial Registry, ChiCTR-ICR-15006787. Registered on 12 July 2015.

**Electronic supplementary material:**

The online version of this article (10.1186/s13063-018-2737-x) contains supplementary material, which is available to authorized users.

## Background

Idiopathic sudden sensorineural hearing loss (ISSNHL) is a common type of deafness in adults and is defined as a sudden hearing loss (≥30 decibels Hearing Level, or dB HL) that develops in less than 72 h and affects three consecutive frequencies [1]. Epidemiological studies from different regions, such as the United States, Sweden, Japan, and Taiwan, suggest that ISSNHL has an annual incidence rate of 5 to 30 out of 100,000 [2–5], another study in Germany confirmed an annual incidence rate of 160 out of 100,000 [6], and the rates are increasing [7]. Concomitant symptoms include a full or blocked ear, vertigo, and tinnitus [2]. Tinnitus can cause extreme anxiety and depression [2]. In China, it was reported that tinnitus was experienced by 70% to 100% of patients with ISSNHL [8]. About one third to two thirds of patients with ISSNHL recover within a couple of weeks [2, 9–11], while after 2 weeks patients would be unlikely to show much recovery [2, 10, 12, 13]. Corticosteroids have been suggested for treatment of ISSNHL within the first 2 weeks [2, 14–16]. However, at present, generally accepted therapies for patients with longer-term ISSNHL are still lacking.

The treatment and prognosis of ISSNHL are closely related to the patient’s audiogram type [17]. According to the German guidelines, ISSNHL has six types [18]: (1) hearing loss at low frequencies, in the range of 250–500 Hz, which has the best prognosis; (2) hearing loss at middle frequencies, around 1000 Hz; (3) hearing loss at high frequencies, above 4000 Hz, which has a poor prognosis; (4) flat type, hearing loss at all frequencies, which also has a poor prognosis; (5) complete/profound deafness, extreme hearing loss at every frequency, which has the worst prognosis; and (6) others unspecified. A multi-center randomized controlled trial (RCT) for a pharmacological treatment in China [19] obtained type-differentiated prognosis data similar to those described in the German guidelines. Some studies showed that ISSNHL with low-frequency drop audiograms has the best prognosis and responds well to treatments [18, 20, 21], complete/profound deafness is difficult to treat [18], and patients with middle-frequency drop audiograms are rare [18]; therefore, ISSNHL patients with flat or high-frequency drop audiograms are more suitable for research than other types. Acupuncture therapy is a significant component of traditional Chinese medicine (TCM). In TCM theory, it is believed that ISSNHL is caused by the Yin-Yang imbalance of internal organs. Acupuncture is considered a useful treatment that brings about balance by stimulating acupoints to activate channels and improve and regulate the functions of Zang-Fu organs, Qi, and Blood according to *Huang Di Nei Jing* (a famous work of ancient TCM literature). Since ancient times in China, there have been reports of acupuncture being used to treat ISSNHL symptoms [22]. Recent studies have suggested that acupuncture may have beneficial effects on ISSNHL [23, 24], but evidence of acupuncture studies that have employed audiograms is limited. Furthermore, prior acupuncture studies did not account for the amount of time elapsed since ISSNHL onset, which is an important prognosis factor that may influence treatment outcomes. Therefore, this randomized controlled clinical trial was designed to evaluate the efficacy and long-term effects of acupuncture as a salvage therapy for patients who have not recovered 2 to 4 weeks after the onset of ISSNHL.

## Methods/Design

### Objective

This RCT will examine the efficacy of acupuncture as an early treatment for ISSNHL patients with flat or high-frequency drop audiograms.

### Study design

This RCT will be undertaken at two sites: Beijing Traditional Chinese Medicine Hospital Affiliated with Capital Medical University and Peking University People’s Hospital. In this study, we will compare the efficacy of Methycobal with or without acupuncture treatment in ISSNHL patients with flat or high-frequency drop audiograms (Figs. 1 and 2). Patient recruitment, hearing testing, baseline assessments, and follow-up evaluations will be conducted in the Department of Otorhinolaryngology at Peking University People’s Hospital. Acupuncture treatments on the study participants will be provided in the Acupuncture and Moxibustion Department of Beijing Traditional Chinese Medicine Hospital Affiliated with Capital Medical University. Both the participants and the acupuncturist will be aware of the treatment groups, but investigators performing assessments will be blinded. The acupuncture treatment will consist of 12 sessions over a period of 4 weeks. The participants will be assessed at baseline, post-treatment (week 4), and follow-up (week 28). This trial will be performed in accordance with the principles of the Declaration of Helsinki (Version Fortaleza 2013). The study protocol has been approved by the Research Ethics Committee of Beijing Traditional Chinese Medicine Hospital Affiliated with Capital Medical University (reference 2014BL-063-02). All participants will sign an informed consent form. The trial will be conducted from September 2018 to June 2020.

**Fig. 1 Fig1:**
[figure not shown]
Trial flow chart. Abbreviation: *THI* Tinnitus Handicap Inventory

**Fig. 2 Fig2:**
[figure not shown]
Chart of trial processes. **refers to “Specific timepoints in this study”

To ensure that the treatments and hearing tests are reliable, two hospitals will participate in this trial: (1) Beijing Traditional Chinese Medicine Hospital Affiliated with Capital Medical University and (2) Peking University People’s Hospital. The Department of Otorhinolaryngology at Peking University People’s Hospital has a sufficient number of patients with acute ISSNHL for the study group and provides standard Western medical treatments. An ear-nose-and-throat doctor will be in charge of patient recruitment, inclusion, hearing tests, and follow-up. The acupuncture treatments will be carried out by highly experienced acupuncturists with a minimum of 20 years of acupuncture experience at Beijing Traditional Chinese Medicine Hospital. The planned acupuncture paradigm was based on the clinical experience of the nationally renowned veteran doctor of TCM, [name], who has been using acupuncture to treat hearing loss for more than two decades. Our team also contains a research methodologist to ensure scientific integrity and feasibility.

### Randomization

Randomization will be accomplished by using SAS 9.1 software (SAS Institute Inc., Cary, NC, USA) and will be carried out by the Research Center of Clinical Epidemiology Affiliated with Peking University Third Hospital. For each of the two ISSNHL types, random allocation sequences will be generated, and opaque sealed envelopes will be created by computer. For both types, the ratio of patients in the treatment group and control group will be 1:1. The envelopes will be attached to one another in numerical sequence, and each envelope will be opened in sequence when a new patient is registered in the trial.

### Participants

#### Inclusion criteria

Ages between 18 and 70;Diagnosis of ISSNHL [1, 25], defined as sudden hearing loss (≥30 dB) in less than 72 h affecting three consecutive frequencies;ISSNHL patients with flat or high-frequency drop audiograms according to pure tone audiometry;ISSNHL began 2 to 4 weeks prior;Hearing improvement of less than 50% since ISSNHL began.

#### Exclusion criteria

Hearing loss from other causes, including congenital deafness, conductive deafness, presbycusis, large vestibular aqueduct syndrome, Meniere’s disease, tumor, or deafness due to systemic genetic diseases;Presence of serious diseases such as insufficiency of heart, liver, and kidney organs or coagulation disorders;Pregnancy or lactating process in females.

### Intervention

Participants in the treatment groups will receive oral Methycobal (0.5 mg three times a day) and verum acupuncture for 4 weeks, while those in the control groups will receive similar Methycobal treatment but without acupuncture. The acupuncture treatment will consist of three sessions per week at the following acupuncture points: Baihui (DU20), Shenting (DU24), Ermen (SJ21), Tinggong (SI19), Tinghui (GB2), Jiaosun (SJ20), Yifeng (SJ17), Waiguan (SJ5), Zhongzhu (SJ3), Zhubin (KI9), Qiuxu (GB40), Taichong (LR3), and Zulinqi (GB41). For the acupuncture treatments, only sterilized single-use needles (Hwato Needles, Suzhou Medical Appliance Factory, Suzhou New District, China) will be used. For limb and abdomen acupoints, 30-gauge needles (0.3 mm in diameter, 40 mm long) will be inserted to a depth of 10 to 15 mm. For head acupoints, 32-gauge needles (0.25 mm in diameter, 25 mm long) will be inserted to a depth of 3 mm. In addition, a special acupuncture manipulation will be used. The acupuncturist will insert a 30-gauge needle (0.3 mm in diameter, 40 mm long) through three acupoints, from Ermen (SJ21) through Tinggong (SI19) to Tinghui (GB2), at an angle of 15° while the patient has his or her mouth open. All needles will be manually manipulated by rotation methods to produce the characteristic sensation known as De Qi. De Qi is a special sensation during acupuncture treatment. When the needle gets to the acupoint, patients always have muscle tenseness around the needle with some feelings such as numbness, distension, soreness, or heaviness. Once De Qi is achieved, needles will be kept *in situ* for 30 min without further manipulations.

### Outcome measures

Audiometry (pure tone hearing test), Word Recognition Score (WRS), and Tinnitus Handicap Inventory (THI) will be used to assess the participants before and after treatment (at weeks 4 and 28). The primary outcome measure will be the effectiveness of hearing improvement, defined as the proportion of patients with an improvement of at least 15 dB in their hearing loss frequency band [25]. For hearing improvement, complete recovery will be defined as hearing level equal to that of the unaffected ear or to hearing prior to ISSNHL [25]. Hearing gains of greater than 30 dB will be considered significant, gains of 15 to 30 dB will be considered effective, and gains of less than 15 dB will be considered ineffective [25]. The secondary outcome will measure the improvements in Pure Tone Average (PTA) (dB HL) [2], in WRS [2] and in THI [26].

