### Patient safety

To ensure patient safety, any adverse events (described as unfavorable or unintended signs, symptoms, or diseases occurring after treatment) related to acupuncture treatment will be noted and reported by patients and practitioners during each patient visit; in addition, all vital signs and adverse events will be measured and recorded at these visits.

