### Statistical analyses

The de-identified outcome data will be analyzed by a statistician blinded to group allocations using the Statistical Package for the Social Sciences V.19.0 statistical software package (SPSS, Chicago, IL, USA). Significant levels will be set at a *P* value of less than 0.05. Data analysis of baseline characteristics and of primary and secondary outcomes will be based on the intention-to-treat principle. The chi-squared test will be conducted for proportions and independent samples. The *t* tests will be analyzed for testing the baseline differences between the two groups. A repeated-measures analysis of variance (ANOVA) will be used to compare the effect of the treatments between the two study groups. Any missing data will be replaced according to the principle of the last observation and carried forward.

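### The response scale counts a worsened ear as merely ineffective, and no stated outcome counts ears that worsen in each arm

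*Protocol article*

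**What the plan says.** The Outcome measures section makes the primary outcome binary, "defined as the proportion of patients with an improvement of at least 15 dB in their hearing loss frequency band". It then sets out a four-step scale. Complete recovery is defined against the unaffected ear or the earlier hearing level. Two middle grades follow: "Hearing gains of greater than 30 dB will be considered significant, gains of 15 to 30 dB will be considered effective". The bottom grade takes everything that is left, since "gains of less than 15 dB will be considered ineffective". No class is given for worsening.

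The same section makes improvement in PTA, WRS and the tinnitus inventory secondary outcomes, with audiometry at baseline, week 4 and week 28. Under Statistical analyses, "A repeated-measures analysis of variance (ANOVA) will be used to compare the effect of the treatments between the two study groups", and missing values are filled by last observation carried forward.

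The Patient safety section covers unfavourable or unintended signs, symptoms or diseases after treatment. Its first clause limits these to events "related to acupuncture treatment will be noted and reported by patients and practitioners during each patient visit". A second clause adds that all vital signs and adverse events are recorded at the visits.

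**The concern.** The Abstract's Discussion paragraph says that positive results could lead to acupuncture being recommended as salvage therapy. The Intervention section places several needles around the ear, one of them passed through three points. Further loss in the treated ear is therefore the harm that bears most directly on such a recommendation. Audiometry planned in both arms would measure it, yet the scale merges it with no change. If acupuncture raised both the share of ears that respond and the share that worsen, the scale would show only the first. The second would have to be inferred from mean scores or from adverse-event reports.

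**Working it through.** **1. The plan's own figure, and whether this point touches it.** Inputs from the Sample size section: 33% v 5% responders, two-sided alpha 0.05, power 0.80.
- Unpooled normal formula: (1.96 + 0.84)² × (0.33 × 0.67 + 0.05 × 0.95) / 0.28² = 26.9, so 27 per group.
- Exact enumeration of the uncorrected chi-squared test at 26 per group: power 0.802, which matches the stated 26.
- Withdrawal: 26 / (1 − 0.15) = 30.6, so 31; 4 × 31 = 124.

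Splitting the non-responders changes neither responder proportion, so 26, 31 and 124 stand.

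**2. What the scale does with a loss.** A change of 0 dB and a change of −20 dB are both below a 15 dB gain. Both are graded ineffective and both are non-responders.

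**3. What mean PTA does with a loss.** If a share w of an arm loses L dB, the arm mean moves by w × L. Illustration with assumed sizes, where responders gain 25 dB and all ears not mentioned stay at 0 dB:
- Acupuncture arm: 33% gain 25 dB and 10% lose 30 dB, so 0.33 × 25 − 0.10 × 30 = 8.25 − 3.0 = +5.25 dB.
- Control arm: 5% gain 25 dB, so 0.05 × 25 = +1.25 dB.
- Difference: 5.25 − 1.25 = 4.0 dB in favour of acupuncture, although one treated ear in ten is 30 dB worse.

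Even without offsetting gains, the mean is a weak detector. The protocol gives no SD for PTA change; 15 to 20 dB is assumed. With 31 per arm:

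| Shift in mean | Arises from | Power, SD 15 | Power, SD 20 |
|---|---|---|---|
| 3 dB | 10% losing 30 dB | 0.12 | 0.09 |
| 6 dB | 20% losing 30 dB | 0.35 | 0.22 |

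**4. What carrying forward does.** A patient who worsens and leaves before week 4 has only the baseline audiogram. The carried-forward change is baseline minus baseline = 0 dB, so the loss also disappears from PTA. A patient who leaves after week 4 keeps the week-4 value at week 28. The plan allows for 31 − 26 = 5 withdrawals per group.

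**5. What adverse-event recording does.** Controls receive no acupuncture, so under the first safety clause they can have no related event. The second clause carries no such limit, but no audiometric threshold makes a decline an event. Treated patients also attend 12 acupuncture sessions that controls do not, so the opportunities for reporting differ.

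**6. What a direct count could show.** With a true deterioration rate of 5%, the probability of at least one case is 1 − 0.95ⁿ. If none is seen, the one-sided 95% upper bound is 1 − 0.05^(1/n).

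| n | Basis | At least one case | Upper bound for 0/n |
|---|---|---|---|
| 52 | 2 × 26 evaluable, audiogram types pooled | 0.931 | 5.6% |
| 26 | evaluable in one group | 0.736 | 10.9% |

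With no withdrawals at all, 62 per pooled arm would give 0.958 and 4.7%. That is the most favourable case.

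**The case against.** A reader might infer from the scale that harm to the treated ear cannot appear in the results. The documents do not support that. PTA and WRS are not cut at 15 dB, so a worse ear enters them as a negative change at weeks 4 and 28. The second safety clause is not limited to related events, and its definition can cover a measured decline.

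A reader might also infer that the primary result is biased, or that needling damages hearing. Neither follows. Every responder endpoint pools its non-responders, and this does not distort the comparison of responder proportions. No section reports hearing loss from needling, and the 10% used above is invented for illustration.

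It can also be said that a table of worsened ears is the kind of detail an article leaves to the full protocol or analysis plan, that the grades follow a cited standard, and that a cut at −15 dB has no source in the article. Much of this stands. The absence of a table is not itself an error, nothing prevents the sponsor from reporting worsening, and the −15 dB cut is only a mirror of the protocol's own threshold. What remains is that the article does fix the categories, and as fixed they merge worsening with no change. The other stated routes show worsening only indirectly.

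**Conclusion.** The point holds in a limited form and is minor. The scale cannot separate loss from no change, and no stated outcome counts ears that worsen. Mean PTA and WRS carry the losses, but responders' gains and carried-forward values can mask them, and the safety wording does not compare the arms fairly. The primary comparison and the sample size are unaffected.

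The masking illustration rests on assumed gains, losses and SD. The precision figures rest on an assumed 5% rate, and the 52-patient figure also on pooling the two audiogram types, although randomisation and sample size are set within type. A count of this size is descriptive: it can reveal a common harm but cannot exclude an uncommon one.

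**What to change.** - Leave the primary responder definition as it is.
- In Outcome measures, split the lowest class into unchanged and deteriorated; for example, deteriorated could mean worse by at least 15 dB in the affected band.
- Report the proportion deteriorated by randomised arm at weeks 4 and 28, within audiogram type and pooled, with confidence intervals. Use observed audiograms, not carried-forward values, and state how many are missing.
- In Patient safety, state that hearing decline is recorded as an adverse event in both arms whatever its presumed relation to acupuncture.
- Reconcile Outcome measures, which has audiometry at week 28, with Blinding, which has telephone interviewers collecting the 28-week follow-up. The week-28 count depends on audiometry being done in person.

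The cost is a few sentences and one descriptive table, with no added patients. Provided week-28 audiometry is in person as Outcome measures implies, no test or visit is added either. The downside for the sponsor is a safety result that might be unfavourable.

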### Blinding

Data managers and statisticians will be blinded throughout the trial. During the study, therapists and data managers will be requested not to communicate with each other about the patient groups. Blinded telephone interviewers will collect the follow-up materials to evaluate the long-term effect of acupuncture at 28 weeks after baseline.

### Sample size

Sample size was calculated on the basis of a single-arm pilot study that showed an effective rate of hearing improvement in 33% of the acupuncture-plus-Methycobal group according to the Chinese sudden hearing loss multi-center clinical study group [19]. We assumed that the effective rate of hearing improvement in the group with only Methycobal was 5%. The difference of the effective rate between the two groups was 28%. This study will be based on 0.8 power to detect a significant difference (α = 0.05, two-sided). In this case, it means that 26 participants will be required for each group, as calculated using PASS 2008. To allow for a 15% withdrawal rate, we plan to enroll 31 participants per group, amounting to a total of 124 participants.

### Patient safety

To ensure patient safety, any adverse events (described as unfavorable or unintended signs, symptoms, or diseases occurring after treatment) related to acupuncture treatment will be noted and reported by patients and practitioners during each patient visit; in addition, all vital signs and adverse events will be measured and recorded at these visits.

### Data management

Two independent researchers blinded to the group allocation will separately enter the data on an Excel spreadsheet after the completion of the case report forms (CRFs). Another independent researcher will crosscheck and compare the two datasets. If different data entry is discovered, it will be compared with the original CRFs to identify any inconsistency. All modifications will be marked on the CRFs. The raw research data will be gathered and saved on a computer. Paper files will be kept in a locked filing cabinet. Electronic documents will be stored in a password-protected computer, and access will be restricted to the principal investigator only. All research documents will be stored for at least 5 years after publication.

### Quality control

All acupuncturists and assessors will be required to undergo special training prior to the trial to guarantee consistent practices. The training program will include diagnosis, inclusion and exclusion criteria, location of the acupuncture points, acupuncture manipulation techniques, and completion of CRFs. Study participants who withdraw from the study will be recorded during the intervention and follow-up periods. This trial will be monitored by the scientific research department of Beijing Traditional Chinese Medicine Hospital. There will be periodic monitoring which will guarantee accuracy and quality throughout the study period.

